## Abstract

**Background:**

At-risk patterns of alcohol use are prevalent in many countries with significant costs to individuals, families, and society. Screening and brief interventions, including with Web delivery, are effective but with limited translation into practice to date. Previous observational studies of the Hello Sunday Morning approach have found that their unique Web-based participatory health communication method has resulted in a reduction of at-risk alcohol use between baseline and 3 months. The Hello Sunday Morning blog program asks participants to publicly set a personal goal to stop drinking or reduce their consumption for a set period of time, and to record their reflections and progress on blogs and social networks. *Daybreak* is Hello Sunday Morning’s evidence-based behavior change program, which is designed to support people looking to change their relationship with alcohol.

**Objective:**

This study aims to systematically evaluate different versions of Hello Sunday Morning’s *Daybreak* program (with and without coaching support) in reducing at-risk alcohol use.

**Methods:**

We will use a between groups randomized control design. New participants enrolling in the *Daybreak* program will be eligible to be randomized to receive either (1) the *Daybreak* program, including peer support plus behavioral experiments (these encourage and guide participants in developing new skills in the areas of mindfulness, connectedness, resilience, situational strategies, and health), or (2) the *Daybreak* program, including the same peer support plus behavioral experiments, but with online coaching support. We will recruit 467 people per group to detect an effect size of *f*=0.10. To be eligible, participants must be resident in Australia, aged ≥18 years, score ≥8 on the alcohol use disorders identification test (AUDIT), and not report prior treatment for cardiovascular disease.

**Results:**

The primary outcome measure will be reduction in the AUDIT-Consumption (AUDIT-C) scores. Secondary outcomes include mental health (Kessler’s K-10), days out of role (Kessler), alcohol consumed (measured with a 7-day drinking diary in standard 10 g drinks), and alcohol-related harms (CORE alcohol and drug survey). We will collect data at baseline and 1, 3, and 6 months and analyze them with random effects models, given the correlated data structure.

**Conclusions:**

A randomized trial is required to provide robust evidence of the impact of the online coaching component of the *Daybreak* program, including over an extended period.

**Trial Registration:**

Australian New Zealand Clinical Trials Registry ACTRN12618000010291; https://www.anzctr.org.au/Trial/Registration/TrialReview.aspx?id=373110 (Archived by WebCite at http://www.webcitation.org/6zKRmp0aC)

**Registered Report Identifier:**

RR1-10.2196/9982

## Introduction

Globally, 5.9% of deaths are attributed to alcohol consumption, and 5.1% of the global burden of disease and injury is attributed to its use [1]. In Australia, alcohol consumption is estimated to cause 3.2% of the total burden of disease. Including harms to nonusers, alcohol consumption contributes about 188,000 disability-adjusted life years, causes 5550 deaths, and costs approximately AU $30 billion/year [2,3]. Australian guidelines provide recommendations for the general adult population specifying that, to reduce the risk of alcohol-related harm over the lifespan, average consumption should be 2 or fewer drinks per day. To reduce the risk of injury from a single occasion of drinking, 4 or fewer drinks are recommended. Further, more stringent recommendations are made for specific groups (eg, pregnant women, those with a family history of alcohol disorders) where the risk of alcohol-related harms is greater [4].

Considered against the 2 main guidelines, in 2016, about 17% of adults were at-risk from their average alcohol consumption, about 26% from their single-occasion use [5], and 37% from either single occasion or average use [6]. Notably, most alcohol-related harm arises from those who consume in an at-risk manner rather than those with an alcohol disorder, with a much greater number of at-risk drinkers than those with disorders [7]. Furthermore, less than 17% of those with an alcohol disorder ever receive treatment for their condition [8], and among those people with less severe alcohol problems, most are unlikely to seek help for their drinking [9].

One approach to addressing alcohol use among those with less severe problems is opportunistic screening and brief intervention (SBI), with the evidence base for the effectiveness of SBI being substantial [10-13]. Under the rubric of SBI, programs can range from a simple screening question combined with a minimal amount of feedback, eg, normative data on alcohol use, through to the use of standardized screening instruments and more intensive interventions that can include components of motivational interviewing and cognitive behavioral therapy. Typically, SBI can be incorporated into a single treatment session in a few minutes but can be several sessions lasting a few hours [14]. However, some, but not all, studies suggest that SBI may be more effective with males than females, and there is an absence of evidence for their effectiveness for those with more severe alcohol use problems [10,11,15]: these people are typically referred for more intensive treatment [16]. Overall, SBI does not appear to have been widely adopted into primary care, and questions remain about its practical implementation, especially within the context of the Australian drinking culture [17,18].

Therefore, alternative approaches to complement existing programs are required. Web-based SBI alcohol interventions have been developed, evaluated, and found to be effective in both college student samples and the general public, excluding students [19,20], with typical effects in the small to medium range (eg, effect size *g=*0.20-0.44) [19,21]. Web-based interventions in their briefest form (eg, single session) typically rely on normative feedback on the self-reported quantity of alcohol consumed, whereas more complex interventions may involve multiple sessions and draw on a range of psychological approaches including motivational enhancement, cognitive behavior therapy, and behavioral control [19,21], similar to the components used in traditional SBI. Nevertheless, Web- or mobile-based SBI has potential advantages over traditional formats, including extended reach, anonymity, timely accessibility, treatment fidelity, the potential to model behavior, and access without the involvement of professionals [21,22]. The evidence to date for the effectiveness of mobile phone–based alcohol interventions is inconclusive, with outcomes ranging from significant improvements on some alcohol measures to significant declines on other measures [23,24].

The benefits of including additional resources to support internet-based interventions are currently unclear. A meta-analysis of internet interventions for depression found a large effect size (*g*=0.78) [25], where all except one of the studies included therapist support. In contrast, a meta-analysis of self-guided internet interventions for depression reported a small effect size (*d*=0.28) [26]. However, a comparison of alcohol interventions found no significant difference between guided (effect size *g*=0.23) versus unguided (effect size *g*=0.20) interventions, although the authors note that this may be due to the small number of guided studies [19]. Nevertheless, benefits have been shown in improving alcohol outcomes (and other health behaviors) from using multiple modes of delivery such as text messages, drawing on theoretical models, and incorporating multiple behavioral change techniques [27,28].

Observational data show that a person’s social network can either increase or decrease their alcohol use [29]. Social networks now include those formed on the internet. These sites range from simple bulletin boards through to virtual lives, but typically allow users to post blogs (text) and images that stimulate discussion and the formation of social groups [30]. The effects of these networks on behavioral change have been evaluated with inconsistent effects found with respect to diet and exercise [31], but to date, the effectiveness of social networks in reducing alcohol consumption has not been determined [30,31], but it is currently being trialed in youth with depression and who engage in binge drinking [32]. In contrast, the persuasive effects of Web-based social networks have been extensively harnessed by alcohol brands to engage with alcohol consumers, with some brands having attracted millions of followers [33,34]. This trial will evaluate the effectiveness of the online coaching component of Hello Sunday Morning’s *Daybreak* program and associated support as a means of reducing alcohol consumption.

Hello Sunday Morning is an Australian social media health promotion movement that asks participants to publicly set a personal goal to stop drinking or reduce their consumption for a set period of time (typically 3, 6, or 12 months [35]), and to record their reflections and progress on blogs and social networks [35,36]. The platform was created in 2010, with the aim of motivating members and holding them accountable by asking them to set a public goal. Further development included gamification features, which were structured games that facilitated participation and engagement with the internet community. Participants in the legacy Hello Sunday Morning platform were recruited by social marketing tactics, leveraging the idea of a movement toward a better drinking culture through social media, word of mouth, and a television commercial. A large portion of members were also recruited through Google AdWords. This platform is no longer actively recruiting participants, and as such individuals are now directed toward the *Daybreak* program.

Initial research conducted on the platform explored the blog content and qualitative reports of change. Text analytics of the blog posts on the platform show that participants typically begin with descriptions of their drinking practices, which over time change to posts reflecting their efforts to change their behavior [37]. Research on the Australian users has found that 84% of participant’s report completing the program time they signed-up to without a slip-up, defined as drinking alcohol before finishing. These participants reported reduced alcohol use and desire to drink alcohol for fun or to relieve tension, and improved mental health [38]. Participants have also reported feeling more positive about themselves, improved productivity and engagement in new activities, as well as new and/or improved relationships and financial savings [39].

Australian users of Hello Sunday Morning are more likely to be female (61%) than male, with most aged less than 50 years (89%). Few (5%) are classified as low-risk alcohol users as assessed by the alcohol use disorders identification test [40] (AUDIT) (score=0-7), with 42% classified in the hazardous or harmful range (AUDIT 8-19) and 53% classified as probably dependent (AUDIT≥20) [35]. Limited follow-up data (n=49) on a subsample of Victorian Hello Sunday Morning participants (n=345) found that the prevalence of probably dependent drinkers fell from 45% at baseline to 7% at 1 month and 24% at 3 months [41].

The aim of the study was to evaluate the effectiveness of the online coaching component of the *Daybreak* program in reducing alcohol consumption via a randomized controlled trial. The *Daybreak* program is a smartphone app developed by Hello Sunday Morning, based on the original Web-based program. *Daybreak* consists of the same social-networking peer-support forum as the Hello Sunday Morning program but also includes clinically based activities known as behavioral experiments and chat-based coaching. The primary hypothesis is that those randomized to receive *Daybreak* including peer-support, behavioral experiments (see *Content of the interventions* for details) plus online coaching, will show a greater reduction in alcohol-related problems that those randomized to just access the *Daybreak* program including peer-support and behavioral experiments (without online coaching). Consistent with the literature, the secondary hypotheses are that greater improvements will be shown for those with lower AUDIT scores (8-19), than those in the higher score category (≥20), and finally, greater improvements are expected for male participants [15,42].

## Methods

### Design

We will use a randomized control design to compare (1) the *Daybreak* program including peer support, behavioral experiments plus online coaching or (2) *Daybreak* program including peer support and behavioral experiments. (The content of the interventions are described below.) Outcome data will be collected at 1, 3, and 6 months post enrollment in the study with all groups receiving the same schedule of assessments (Figure 1). Australian ethical guidelines preclude the use of placebo (no treatment) control groups where a risk has been identified and there are existing treatments/interventions [43].

### Participants and Randomization

All new registrants to *Daybreak* will receive information about the study: it is anticipated that no additional advertising will be required. To be eligible for the study, participants must be aged 18 years or older, score 8 or more on the [44] AUDIT, and be resident in Australia. Participants also require a valid email address and access to the internet. We will exclude those who have ever received treatment for cardiovascular disease, due to the risks for this latter group [45]. In addition, the screening questions include the P4 suicidality screening survey [46]. Those scoring above minimal risk will still be eligible for the study but will receive details of a national, 24-hour crises support line (lifeline).

Regardless of the group to which they are randomized, those scoring 20 or more on the AUDIT (probable dependence) will be eligible for inclusion in the study but will also be advised to seek in-person guidance from their general practitioner or other clinician before reducing their alcohol consumption, to minimize the risk of serious complications from alcohol withdrawal. Given the large sample, simple fully automated randomization will be implemented. Participants will be blind to their group allocation—all will receive an active treatment. Participants access the platform by logging in with their email address and password.

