### Procedure

Enrollment and intervention procedures will be self-guided. Individuals who register to start the *Daybreak* program generate a username and password, and they will then be asked if they are interested in participating in the project. For those affirming, they will then receive the full study description and be asked for active consent (clicking on a button). They will then be screened for eligibility by completing a Web-based survey, before being randomized. Those that are screened as ineligible are returned to the *Daybreak* on-boarding procedure (Multimedia Appendix 1) and notified of their ineligibility, and they are provided with relevant details of the crisis support services. Participants have unlimited access to their respective areas, and those randomized to *Daybreak* plus coaching can access a health coach (available from 7 AM to 7 PM local time Monday-Friday).

At 1, 3, and 6 months, participants will be emailed and texted a link to the follow-up survey. If they do not complete the survey, a repeat text message will be sent 1 week later. Following this, a research assistant (blind to group allocation) will call the participants to remind them to complete the survey on a maximum of 3 occasions and provide the link again via email or text message if requested during the call. At each wave, participants will be invited to enter their details for a prize draw to win an iPad 2. Participants do not have to complete the survey to enter the draw, but the link to the prize draw will be at the end of the surveys. The study received institutional ethics approval (2017-0855) and has been registered with the Australian and New Zealand Clinical Trials Registry trial number ACTRN12618000010291.

Recruitment will be conducted over 10 months from February to November 2018 or until the desired sample size is obtained. New registrants either directly download the *Daybreak* app from the App Store, or reach the Hello Sunday Morning website (where they are directed to download it) by searching Google, or by clicking from other websites such as healthdirect.gov or other health service directories, or by clicking through from the Hello Sunday Morning email newsletter.

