The fourth one is health coaches. All health coaches meet the low-intensity mental health guidelines set by the Australian Government Department of Health [58]. Specifically, this includes a minimum certificate IV in a mental health or community services discipline. The clinical team of health coaches at Hello Sunday Morning all meet this minimum criterion, as well as having specific alcohol and other drug training and experience. Some coaches are registered General and Clinical Psychologists.

Health coaches are required to undertake in-house training, which includes modules on health coaching and how it differs from therapy, ethical considerations when providing Web-based services, alcohol facts and management strategies, forming connections during online support, motivational interviewing, case studies and ethical dilemmas, coaching procedures, risk management, as well as platform-specific training modules. They undergo a period of supervision on initial interactions with participants and then periodically receive feedback from a senior health coach. Health coaches also participate in fortnightly peer supervision for case discussion and receive individual supervision with an Australian Health Practitioner Regulation Agency–approved supervisor who is a clinical psychologist, when needed.

Health coaches partner with members to help them set and reach goals for satisfying and healthy lives. The coaching service is conducted via real-time chat-based messaging on a secure platform. Health coaches again use cognitive behavioral therapy, motivational interviewing, and acceptance and commitment therapy techniques. Coaches tailor support and the approaches used to suit the member’s needs.

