The study raises some ethical issues, particularly with respect to the age of participants and the adverse outcomes that can occur in unsupported withdrawal from alcohol use. Although we will ask participants to confirm that they are aged 18 years or older, and thus able to provide informed consent, the noninvasive nature of the intervention reduces the concerns about underage participants entering the trial. To mitigate against the potential for unsupported severe withdrawal symptoms, we will advise participants considered to be at higher risk to seek professional guidance before reducing or ceasing consumption.

The study relies on self-reported data, which is common for Web-based alcohol interventions [19]. Other than the identification of acute intoxication, objective quantification of alcohol use even over a limited period (such as 7 days) is difficult. None of the standard clinical markers (eg, gamma glutamyltransferase) perform adequately as screening tests for this task, particularly with women and at intermediate levels of alcohol use, or provide a quantification of the amount of alcohol consumed [61]. Therefore, we believe that there is no other method of determining the extent of alcohol use that is more reliable than self-report, without implementing far more demanding procedures, such as twice daily breath testing, as used in some judicial programs [62].

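### The protocol calls participants blind to allocation, but the arms differ by live human coaching that its recipients can see, and every outcome is self-reported

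*Protocol article*

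**What the plan says.** Under Participants and Randomization the protocol article states: "Participants will be blind to their group allocation". The reason attached is that both arms are active. It adds no qualification and no other reason.

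The contrast under test is given in the Introduction: "The aim of the study was to evaluate the effectiveness of the online coaching component". The Design section confirms that peer support and behavioral experiments are common to both arms and that online coaching is the only difference.

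Content of the Interventions lists health coaches as the fourth way in which the program works and says: "The coaching service is conducted via real-time chat-based messaging on a secure platform". According to Procedure, only those randomized to coaching can reach a coach, on weekdays during set hours, and each arm uses its own area of the platform.

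Before eligibility screening and randomization, those who express interest are informed: "they will then receive the full study description and be asked for active consent".

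On measurement, the Discussion says: "The study relies on self-reported data". The only other blind role described is the research assistant who telephones non-responders to remind them of the survey.

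**The concern.** Blinding to allocation requires that participants cannot tell which arm they are in. Two arms can both be active and still be easy to tell apart, so the reason given does not support the claim.

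In this trial the participant is in effect the outcome assessor. Someone who knows they have had a coach may report drinking differently from someone who has not, whatever they actually drank. If the trial is reported as participant-blind, readers and systematic reviewers will take this bias to be excluded by design and will understate the risk of bias. The planned effect is small (d=0.2), so a modest reporting difference could matter to the conclusion.

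**Working it through.** The protocol attaches no figure to its blinding statement, so there is none to reproduce. The check compares the sections, and a short calculation then illustrates sensitivity.

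**Can a participant tell the arm?**

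- *Coached arm.* The participant has access to live chat with a person. The article describes nothing that could hide this from them.
- *Uncoached arm.* No sham coach or attention control is described, so there is no chat with a coach. Whether these participants know that something was withheld depends on the wording of the study description, which is not shown.
- *Result.* Blinding to allocation fails for the coached arm whatever the study description says. For the uncoached arm it is undetermined. The protocol's statement covers all participants.

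**Does anything else protect the outcomes?**

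- *Primary outcome.* AUDIT-C consists of three questions answered by the participant through a survey link.
- *Secondary outcomes.* The drinking diary, K-10, days out of role, health resource checklist, sleep item, exercise questionnaire, quality of life and adverse events checklist are all completed by the participant.
- *Research assistant.* This person is blind but only reminds participants and rates nothing.
- *Discussion.* It defends self-report as the most reliable practicable way to quantify alcohol use. It does not consider that reporting may differ between arms.

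**Illustration of size.**

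Inputs from Sample Size: 467 recruited per arm, 35% lost to follow-up, r=0.5 between repeated measures, planned effect d=0.2. Assumed, not in the documents: no true effect, and a reporting difference b between arms of 0.05 or 0.10 SD (a quarter or half of d=0.2).

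1. Completers per arm: 467 × 0.65 = 303.55, about 304.
2. The Analysis section tests a time-by-group interaction, and the Abstract includes baseline among the analyzed time points. The matching simple contrast is change from baseline, with variance 2(1 − r) = 2(1 − 0.5) = 1.0 in SD² units.
3. SE of the difference between arms: √(2 × 1.0/304) = 0.081.
4. Two-sided rejection probability: 1 − Φ(1.96 − b/SE) + Φ(−1.96 − b/SE).

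| Assumed b (SD) | b/SE | Rejection probability |
|---|---|---|
| 0 | 0 | 5% |
| 0.05 | 0.62 | 0.0895 + 0.0050 = 0.0945, about 9% |
| 0.10 | 1.23 | 0.2336 + 0.0007 = 0.2343, about 23% |

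The formula is two-sided, so the direction of the reporting difference does not alter these figures. They approximate the planned mixed model, which would also use partial follow-up.

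**The case against.** The strongest defence is that the consent text is not shown. Recruits are new registrants, and coaching is described as an ordinary part of Daybreak. A coached participant may think they simply have the standard product, and an uncoached one may not know that coaching exists. The sentence could then mean that participants are not told what the contrast is. This is possible, and it limits what can be said: a reader might infer that both arms certainly know the contrast and the hypothesis, and the article does not establish that. It does not rescue the sentence, because coached participants still know they have a coach and the protocol states no such narrower meaning.

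Outcomes are collected by survey link and not by the coach, which should reduce pressure to please the coach. That stands as partial mitigation, but it does not remove knowledge of having been coached.

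Blinding participants to a human coaching add-on is rarely feasible. That is also fair. The criticism is of the claim to have achieved it, not of the design for lacking it.

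A reader might also put a larger number on the bias. A baseline-adjusted SE of √(0.75 × 2/304) = 0.070 gives about 11% and 30% for the same assumed biases. The protocol describes a time-by-group interaction, for which the change contrast is the closer match, so the lower figures are used here.

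**Conclusion.** The statement is wrong as written. The design does not blind participants to allocation. Any blinding is at most to the hypothesis or to the other arm's content, and only if the study description supports it. With every outcome self-reported, a between-arm difference in AUDIT-C may partly reflect differential reporting, and the protocol does not acknowledge this.

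The size of any such bias is unknown. The range of about 9% to 23% rests on an assumed 0.05 to 0.10 SD reporting difference, 304 completers per arm, r=0.5 and a change-score approximation. It shows sensitivity and estimates nothing about this trial.

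Two further inferences are not supported. One is that observed effects below some threshold should be discounted; the documents give no basis for choosing one. The other is that the analyst is blind, so that some blinding of the evaluation remains; the article says this only of the research assistant. The conclusion does not depend on the calculation, and it calls for no change to the interventions, sample size or analysis model.

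**What to change.** Replace the blinding sentence with: *Participants are not blind to allocation [if the study description supports it: but are not told the study hypothesis]; the research assistant who makes reminder calls is blind.* Claim analyst blinding only if the sponsor confirms it.

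Add to the Discussion's paragraph on self-report, as a limitation, that a between-arm difference in AUDIT-C may partly reflect differential self-report by participants who know whether they were coached.

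A perceived-allocation item in the 6-month survey is optional. Enrollment has already started, so it would change the instrument mid-trial and may need ethics review. Answers given at 6 months are also colored by perceived benefit, so they cannot cleanly separate unblinding from efficacy.

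The required changes are to wording only. Their cost is that the design is described less favourably.
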